## Method/design

### Study design

This is a prospective, randomised, placebo-controlled, cross-over, double-blind, single-centre study over a period of 36 months.

Each patient included will participate in three visits.

Visit 1 (V1): inclusion and baseline assessment visit. Patients who fulfil all the inclusion and non-inclusion criteria and who have signed informed consent will be included in the study. During this visit, all the clinical and functional evaluations, the instrumented gait analysis and instrumented balance task will be carried out. The patient will also complete all the clinical scales and self-evaluation questionnaires. Furthermore, blood samples will be taken in order to carry out genetic studies and identify carriers of the Val66Met polymorphism in the brain-derived neurotrophic factor gene, since Val66Met reduces the effects of all types of non-invasive brain stimulation [48, 49].

Visits 2 and 3 locomotion/balance (V2 and V3): anodal tDCS or placebo visits. During these visits, before the cortical stimulation (anodal or placebo), all the functional and clinical data will be collected. A 3D gait analysis and instrumented balance task will be carried out before and during the 30 min of stimulation, as well as immediately after the end of the stimulation and 30 min later. Functional and clinical data will be collected again following the stimulation. The order of the placebo and anodal tDCS visits will be randomised. The visits will be 7 days apart. The study schedule is shown in Fig. 1 and the evaluations conducted during the three visits are shown in Table 1.

**Fig. 1 Fig1:**
[figure not shown]
The study schedule. Study timeline from the inclusion visit (V1) to the end of the study (V2 and V3). Patients will undergo clinical evaluations (CLI), gait analysis (GA) and an instrumented balance evaluation (BAL)

**Table 1 Tab1:** Tests and evaluations during each visit

Test	V1	V2	V3
Inclusion/exclusion criteria	X		
Informed consent	X		
Randomisation	X		
Stimulation (anodal or placebo)		X	X
Evaluation of passive range of motion (manual goniometer)	X	X	X
Evaluation of spasticity (modified Ashworth Scale)	X	X	X
Evaluation of strength (Medical Research Council)	X	X	X
Gait quality: ABILOCO scale	X		
Berg Balance Scale	X		
FIM	X		
SF36	X		
Time to ascend and descend a flight of ten 11-cm-high stairs	X	X	X
Timed Up and Go Test	X	X	X
Six-minute Walk Test	X	X	X
Ten-metre Timed Walk – maximal	X	X	X
Box and Block test	X	X	X
3D gait analysis	X	X	X
3D trajectory tracking	X	X	X
Instrumented gait and balance tests	X	X	X

Abbreviations: The Short Form Health Survey (SF36) Functional Independence Measure (FIM)

### Stroke diagnosis

Participants will be individuals with chronic stroke (more than 6 months). For the purpose of this study, stroke is defined, according to the World Health Organisation as ‘a rapid onset event of vascular origin reflecting a focal disturbance of cerebral function, excluding isolated impairments of higher function and persisting longer than 24 h’ [50].

### Inclusion criteria

Patients will be included if they fulfil the following inclusion criteria: adult man or woman aged 18 years or older, with hemiparesis following unilateral hemispheric cerebral lesions of vascular origin more than 6 months previously, able to walk for 10 min non-stop with no gait aids, having provided informed consent.

### Exclusion criteria

Patients will be excluded if they have any of the following: a pacemaker, claustrophobia (for the magnetic resonance imaging (MRI)), aphasia or cognitive difficulties that could interfere with comprehension of instructions, neuro-orthopaedic surgery to the lower limb less than 6 months previously, concomitant progressive disease, epileptic fit less than 1 year prior to the date of inclusion, intracerebral metal clip, non-affiliation to the social security regime, being under guardianship.

### Participant recruitment

Patients will be recruited from inpatient wards and outpatient consultations in the physical medicine and rehabilitation department of our university hospital. Once potential patients have been identified, the investigator or his assistant will approach them to provide information about the study, both in written and verbal form, only after the patient has indicated interest in participating.

### Randomisation method

Randomisation will be carried out at the end of the inclusion visit. A randomisation list will be uploaded on a dedicated server (CleanWeb) using ‘Randoweb’ software and made available on a website for centralised randomisation.

### Blinding

In order to ensure patient blinding, one electrode will be placed over the motor cortex of the affected hemisphere and one additional electrode on the contralateral orbit in accordance with the placement procedures described below. When the current is initiated, patients traditionally report a sensation of pruritus under the active electrode for 2 min. In order to mimic this sensation, in the placebo condition, the patient will receive 120 s of current (which is less than the 3 min necessary to induce effects [33]).

In order to maintain the blinding of the investigator and assistant, an independent physician will set up the tDCS in either anodal or placebo mode, this physician will not be involved in recording, collecting or processing the data.

### Intervention

Anodal tDCS: the anode will be placed over Cz of the international electroencephalogram (EEG) 10–20 system and the cathode above the contralateral eye [51]. Rectangular electrodes (25 cm^2^) inserted in a saline-soaked sponge will be used. The stimulation intensity will be set to 2 mA for 30 min with a current density of 0.07 C/cm^2^. These stimulation criteria are well below the threshold for tissue damage [52]. The target intensity will be reached in 8 s and, at the end of the 30 min, it will be reduced over 8 s.

Placebo tDCS: the electrodes will be positioned exactly as for anodal tDCS; however, the current will only be delivered for 150 s, 120 s at the beginning and 30 s at the end of the 30 min in order to mimic the possible sensation of pruritus perceived during the increase and decrease in current intensity. Nitsche and Paulus (2000) previously showed that 3 min of tDCS were necessary to induce a post effect [33].

There will be an interval of 7 days between the two stimulation conditions.

### Characterisation of patients (inclusion visit only)

Several evaluations will only be carried out at the inclusion visit, in order to characterise the patients: the ABILOCO scale composed of 13 items to evaluate gait quality; the Berg Balance Scale, an objective measure of balance and risk of falls consisting of 14 items; the Functional Independence Measure (FIM), a measure of independence in activities of daily living; and The Short Form (36) Health Survey (SF36) questionnaire of health status that is often used as a measure of quality of life.

### Primary outcomes

#### Before, during, immediately after, and 30 min after tDCS cessation

Variability of the COM

As previously indicated, the variability of COM displacement is a strong marker of dynamic stability during locomotion and it is altered in patients with stroke.

The primary outcome measure of this study is thus the assessment of the variability of the displacement of the COM during gait and during trajectory tracking over the ground, evaluated by 3D gait analysis and the variability of the displacement of the COP during a static-balance task on a force platform. It will be recorded once during the inclusion visit then four times during the stimulation visits: before, during, immediately after and 30 min after cessation of stimulation. A reduction in the variability of COM displacement should result in an improvement of spatiotemporal, kinematic and kinetic gait parameters.

The 3D gait analysis will be conducted with a 3D optoelectronic system (Motion Analysis Corporation, Santa Rosa, CA, USA, sampling frequency 100 Hz) with eight optoelectronic cameras. Thirty markers will be placed on the patient’s body (following the Helen Hayes model commonly used by the biomechanical community for gait analysis [53]). The relative displacement of each segment will be calculated from these coordinates (flexion/extension, abduction/adduction, internal/external rotation). The marker trajectories will then be filtered using a fourth-order zero-lag Butterworth low-pass-filter, with a 6-Hz cut-off frequency [54]. The data from two force platforms combined with the kinematic and anthropometric data will be used to evaluate the displacement of the COP and COM during gait and balance tasks.Instrumented gait task

Ten trials of gait at a comfortable speed and 10 trials at maximal speed will be recordedInstrumented balance task

Three balance conditions of differing complexity will be evaluated to assess the effects of tDCS on postural capacity:Static (i.e. orthostasis): in standing, with both feet on a force platform separated by a standardised distance, patients will be asked to remain as immobile as possible for 60 s. Two sensory conditions will be tested: with (eyes open: EO) and without (eyes closed: EC) visual informationAnalysis of the trajectory of the centre of foot pressure coupled with the kinematic analysis of the body segments recorded by an optoelectronic movement analysis system will allow us to determine the characteristics of the stability of bipedal posture in these different sensory conditionsStatic-dynamic transition (i.e. initiation of the first step): while standing, with both feet on a force platform, patients will be asked to initiate 10 steps with the paretic foot and 10 steps with the non-paretic foot. Analysis of the trajectory of the centre of foot pressure coupled with the kinematic analysis of the body segments recorded by an optoelectronic movement analysis system and electromyography (EMG) analysis of the muscles involved will allow us to determine the characteristics of postural stability during the transition from a static to a dynamic posture

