**Methods/design:**

This is a prospective, randomised, placebo-controlled, double-blinded, single-centre, cross-over study over 36 months. Forty patients with chronic stroke will be included. Each patient will participate in three visits: an inclusion visit, and two visits during which they will all undergo either one 30-min session of transcranial direct current stimulation or one 30-min session of placebo stimulation in a randomised order. Evaluations will be carried out before, during and twice after stimulation. The primary outcome is the variability of the displacement of the centre of mass during gait and a static-balance task. Secondary outcomes include clinical and functional measures before and after stimulation. A three-dimensional gait analysis, and evaluation of static balance on a force platform will be also conducted before, during and after stimulation.

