The main aim of this randomised controlled trial is, therefore, to show that a single session of anodal tDCS can decrease the variability of the displacement of the COM during gait, during a static-balance task and during a gait-initiation and obstacle-crossing task in patients with chronic stroke. According to Bikson et al. (2013), tDCS specifically enhances the task performed during the stimulation [47]. Therefore, we will assess the primary outcomes before, during and after the tDCS.

The secondary objectives are:Firstly, to show that compared to placebo condition, anodal tDCS improves spatiotemporal, kinematic and kinetic gait parameters, as well as the ability to follow a trajectory or cross an obstacleSecondly, to show that, compared to a placebo condition, anodal tDCS improves performance on functional tests and clinical tests (assessment of strength and spasticity) that will be not performed during the stimulation. This will determine whether anodal tDCS only improves tasks executed during the stimulation, or if the effects can transfer to other tasks (for example, the paretic upper limb)Thirdly, to show if changes induced by anodal tDCS are correlated with the patient’s profile (based on clinical evaluation scales, performance on functional tests and the time since lesion onset)

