### Secondary outcomes

#### Before, during, immediately after and 30 min after tDCS cessation

The same 3D gait analysis described above will be used to evaluate the effect of anodal tDCS on kinematic and kinetic gait parameters, trajectory tracking and obstacle crossing.Gait analysis:

Ten trials of gait at a comfortable speed and 10 trials at maximal speed will be recorded in order to evaluate the spatiotemporal, kinematic, kinetic and EMG parameters during gait. Surface EMG will also be performed during the gait analysis. These data will be used to define the patterns of activation of the principle superficial muscles (rectus femoris, vastus lateralis, medial hamstring, biceps femoris, tibialis anterior, medial gastrocnemius and soleus) activated during gait. The EMG data will be used to quantify the activity of the agonist and antagonist muscles (of the hip, the knee and the ankle) in order to determine a possible interaction between muscle activity, variability of COM displacement and joint kinematicsInstrumented path-following task (trajectory tracking)

From a standing start, the patient will be asked to follow a 2.5-cm-wide strip on the ground, walking with one foot on each side of the strip. The 8-m-long strip will be positioned so as to form a figure of 8. The distance of the trajectory of the COM during this task, as well as its oscillations with respect to the strip, will be quantified. The trajectory length and COM oscillations before, during, immediately after and 30 min after cessation of stimulation will be compared to determine whether the patients’ dynamic stability during the task has been modified by the tDCSInstrumented evaluation of obstacle crossing

From a standing start with one foot on a force platform, the patient will be asked to step over an 11-cm-high, 2-m-wide bar leading with the paretic limb (three trials) and the non-paretic limb (three trials). The time to cross the obstacle, the number of contacts with the obstacle and the height of the foot relative to the obstacle will be determined, as well as the trajectory of the centre of pressure (COP) until the foot is lifted. The patient will be asked to stand still after crossing the obstacleBefore and after the tDCS: clinical evaluation

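### The article gives four incompatible statements of the primary outcome, lists trajectory tracking as both primary and secondary, and has no rule for which result decides the trial

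*Protocol article*

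**What the plan says.** Four places in the article state what the trial is primarily meant to show.

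- **Abstract, Methods/design:** "The primary outcome is the variability of the displacement of the centre of mass during gait and a static-balance task".
- **Background, main aim:** a reduction in the variability of "displacement of the COM during gait, during a static-balance task and during a gait-initiation and obstacle-crossing task". The paragraph then speaks of primary outcomes in the plural. Trajectory tracking is not named.
- **Primary outcomes:** "the assessment of the variability of the displacement of the COM during gait and during trajectory tracking over the ground", plus "the variability of the displacement of the COP during a static-balance task on a force platform". Gait initiation is described further down under this heading but is not in the definition. Obstacle crossing does not appear.
- **Discussion, Impact:** lower COM variability in walking, quiet standing and the static-dynamic transition. Neither trajectory tracking nor obstacle crossing is named.

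Two further places give secondary status to tasks named above. The first secondary objective in the Background includes following a trajectory and crossing an obstacle. The Secondary outcomes section uses the same gait analysis "to evaluate the effect of anodal tDCS on kinematic and kinetic gait parameters, trajectory tracking and obstacle crossing".

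The Statistical analysis section derives 39 patients (40 to be included) for 90% power at α = 0.05. It starts from a 99.5 cm difference in trajectory length between stroke patients and healthy subjects in the Timed Up and Go. Analysis of outcome measures sets a two-sided 5% level for all tests and names a Scheffé adjustment for multiple comparisons.

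**The concern.** A confirmatory trial needs a primary question that is the same wherever it is stated. Here the set of primary tasks changes from section to section, and so does the quantity measured in one of them. Once the data are known, a favourable result in any of the listed tasks could be presented as primary with support from some section, and an unfavourable one could be called secondary with support from another. The false-positive risk of the headline claim is then not controlled. The 90% power, which was derived for a single comparison, also cannot be assigned to a particular result.

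**Working it through.** **1. The statements side by side** (a dash means not named)

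| Place | Gait | Static balance | Gait initiation | Obstacle crossing | Trajectory tracking |
|---|---|---|---|---|---|
| Abstract | COM | COM | – | – | – |
| Main aim | COM | COM | COM | COM | – |
| Primary outcomes (definition) | COM | COP | – | – | COM |
| Discussion, Impact | COM | COM | COM | – | – |
| Secondary objectives and Secondary outcomes | other parameters | – | – | secondary | secondary |

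No two of the four primary statements coincide. COM variability in gait is the only entry that appears in all four with the same measure.

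The double listing of trajectory tracking is not one task with two clearly different endpoints. The secondary measures are COM path length and COM oscillation about the strip, close to the COM variability named as primary. The Appendix does not settle COM against COP, because it gives formulas for both in the balance tasks.

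The number of primary tasks is therefore 2 (Abstract), 3 (Primary outcomes; Discussion) or 4 (main aim). It would be 3 for the main aim if gait initiation and obstacle crossing are read as one combined task.

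**2. The plan's own sample size**

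Inputs: N = 39, power 90%, two-sided α = 0.05, and a 50 to 60% reduction of 99.5 cm, which is 49.75 to 59.7 cm. The SD comes from the cited study and is not given, so 39 cannot be reproduced exactly. It can be solved backwards for one paired comparison.

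- Normal approximation: d = (1.960 + 1.282)/√39 = 0.519. The noncentral t gives d = 0.533.
- Implied SD of the paired difference: 49.75/0.533 ≈ 93 cm to 59.7/0.533 ≈ 112 cm.
- For comparison, by noncentral t, d = 0.5 needs 44 patients and d = 0.8 needs 19.

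So 39 fits the stated moderate-to-large effect for **one** paired comparison.

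**3. What several primaries would do (illustration)**

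Assume k tasks, each tested at two-sided 5%. If any one counts as success and the tasks are independent, the family-wise error is 1 − 0.95^k. The correlated values come from simulating equicorrelated normal statistics, with ρ assumed. The Bonferroni columns use α/k and d = 0.533 per task. The last column is the power if all k must succeed at 5% each, under independence with 40 patients (0.907^k, where 0.907 is the single-test power).

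| k | Error, independent | ρ = 0.5 | ρ = 0.8 | N for 90% power, Bonferroni | Power per test at N = 40, Bonferroni | Power if all must succeed |
|---|---|---|---|---|---|---|
| 2 | 9.8% | 9.1% | 7.9% | 47 | 85% | 82% |
| 3 | 14.3% | 12.4% | 9.7% | 51 | 80% | 75% |
| 4 | 18.6% | 15.5% | 11.4% | 54 | 77% | 68% |

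Under an any-one rule the error rate rises above 5%. Under an all-must-succeed rule the power falls. The article states neither rule.

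**The case against.** The strongest defence is that an article condenses a fuller protocol. The choice of gait speed, visual condition, leg and time point is commonly left to that document or to the analysis plan. This stands: the absence of a named speed or time point is not, taken alone, an error in the article. It does not cover the conflict between task lists or the switch from COM to COP. An analysis plan that chose one version would still contradict the others.

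Several stronger readings are tempting but not supported.

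- *That 15 to 27 results could be called primary.* That count multiplies tasks by speeds, visual conditions, legs and three time points. The plan names repeated-measures ANOVA and/or analysis of covariance with Scheffé-adjusted comparisons, so time, and possibly speed or vision, can be factors in one model. The Scheffé adjustment is not tied to a primary family, however, and does not say which task decides.
- *That obstacle crossing is double-listed as clearly as tracking.* It reaches primary status only through the main aim, and its secondary measures (crossing time, contacts, foot height, COP path) include no COM variability.
- *That the Secondary outcomes section is itself a statement of the primary outcome.* It is not. It matters only because it gives secondary status to tasks that are primary elsewhere.
- *That a balance condition is missing because* "Three balance conditions of differing complexity will be evaluated" *and only two are described.* Eyes open, eyes closed and step initiation can be counted as three, and the list layout was lost in the text available.

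Finally, several primary outcomes can be legitimate, and nothing in the article says that success on any one is enough. The error rates above therefore describe an assumed rule and not a stated one.

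**Conclusion.** The point holds as a contradiction within the text. Four statements of the primary outcome disagree on the tasks, and one of them differs on the measure used for static balance. Trajectory tracking is both primary and secondary with nearly the same measure. Two to four tasks are primary with no decision rule, while the sample size matches one comparison.

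The size depends on the rule eventually applied. With any-one success at 5% each, the error is 9.8% to 18.6% for two to four independent tasks, and about 8% to 11% at an assumed correlation of 0.8. These figures are illustrative; the sample-size comparison also rests on the back-solved d of 0.533. The contradiction itself needs no assumption. It should be resolved before unblinding, because the trial's conclusion can depend on which section is followed.

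**What to change.** Before unblinding, adopt one primary definition that states the task, COM or COP, the condition and the time point. There are two acceptable forms:

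- **A single primary endpoint.** One example is the anodal-minus-placebo difference in COM variability during gait, at one named speed and time point. Gait is the task type behind the sample size and the only entry common to all four statements.
- **A fixed list of primaries** with a stated hierarchy or alpha split.

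In either form, list every other task as secondary only, and use the same wording in the Abstract, main aim, secondary objectives, Primary and Secondary outcomes, Statistical analysis and Discussion.

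The trial was ongoing at submission, so this is an amendment to wording and needs no new measurements. With a single endpoint, some tasks lose primary status. With an alpha split, the stated 90% power must be restated per test: with Bonferroni, 40 patients and d = 0.533, it would be about 85%, 80% or 77% for two, three or four primaries.

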### Secondary outcomes

#### Before, during, immediately after and 30 min after tDCS cessation

The same 3D gait analysis described above will be used to evaluate the effect of anodal tDCS on kinematic and kinetic gait parameters, trajectory tracking and obstacle crossing.Gait analysis:

Ten trials of gait at a comfortable speed and 10 trials at maximal speed will be recorded in order to evaluate the spatiotemporal, kinematic, kinetic and EMG parameters during gait. Surface EMG will also be performed during the gait analysis. These data will be used to define the patterns of activation of the principle superficial muscles (rectus femoris, vastus lateralis, medial hamstring, biceps femoris, tibialis anterior, medial gastrocnemius and soleus) activated during gait. The EMG data will be used to quantify the activity of the agonist and antagonist muscles (of the hip, the knee and the ankle) in order to determine a possible interaction between muscle activity, variability of COM displacement and joint kinematicsInstrumented path-following task (trajectory tracking)

From a standing start, the patient will be asked to follow a 2.5-cm-wide strip on the ground, walking with one foot on each side of the strip. The 8-m-long strip will be positioned so as to form a figure of 8. The distance of the trajectory of the COM during this task, as well as its oscillations with respect to the strip, will be quantified. The trajectory length and COM oscillations before, during, immediately after and 30 min after cessation of stimulation will be compared to determine whether the patients’ dynamic stability during the task has been modified by the tDCSInstrumented evaluation of obstacle crossing

From a standing start with one foot on a force platform, the patient will be asked to step over an 11-cm-high, 2-m-wide bar leading with the paretic limb (three trials) and the non-paretic limb (three trials). The time to cross the obstacle, the number of contacts with the obstacle and the height of the foot relative to the obstacle will be determined, as well as the trajectory of the centre of pressure (COP) until the foot is lifted. The patient will be asked to stand still after crossing the obstacleBefore and after the tDCS: clinical evaluation

Passive range of motion (manual goniometer) of the hip, knee and ankle joints of the hemiparetic lower limb, spasticity (modified Ashworth Scale) and muscle strength (Medical Research Council) of the hip, knee and ankle flexor and extensor muscles of the hemiparetic lower limb will be evaluated before and after stimulation. Functional gait and balance scales and functional tests will also be evaluated (described below) before and after stimulationFunctional clinical tests

Four functional clinical tests of gait and balance will be evaluated: the time to ascend and descend a flight of ten 11-cm-high stairs; the Timed Up and Go Test that evaluates postural transitions, gait, balance, turn-around and risk of falls; the Ten-metre Timed Walk that evaluates gait speed will be carried out at maximal speed; and the 6-minute Walk Test that evaluates the distance walked in 6 min, providing an indication of endurance capacityTests to verify if the upper limb is affected by anodal tDCS

The Box and Block test evaluates unilateral gross manual dexterity. It will be carried out in order to verify if the effects of the stimulation are limited to the motor tasks carried out during the stimulation or also occur in similar tasks such as functional tests (mentioned above) or tasks carried out by another limb.

